**Fig. 3 Fig3:**
[figure not shown]
Examples in which background is removed from the initial image (**A**), intermediary images are obtained for one side (**B-F**), and either both views are kept (**G**), or the Doppler color side is used alone (**H**)

#### III. Frame Classification

As previously stated and illustrated in Fig. 2, the deep learning model needs another class to be learned, apart from the ones illustrated in Fig. 1. This class should not contain any key plane; hence we labeled it *other*, meaning it is unimportant (not informative). It will be appointed to make the machine recognize the key features from the sweeping, where the majority represents noise or transition between the views. They do not belong to any of the key planes, and the model should appropriately identify them as not informative. Contrarily, if the model were trained without the *other* class, for each frame that does not contain a particular plane, the algorithm would feel forced to label it with one of the classes of interest, even if that image does not represent anything of value for the detection.

Accordingly, the saved US video files will allow the automatic extraction of the frames that do not confidently present any of the key planes, i.e., the *other* samples. The images extracted from the video frames by the OB-GYN experts will be used for comparison with the frames from the video files, and, when the similarity is below a certain threshold, the frames will be considered distinct enough from the images of the key planes and will be saved to the *other* folder. The number of such non-important images can be very high, but it will be controlled by establishing an adequate number of samples, i.e., around 30% more samples than in the class with the most images. The higher the quantity of the images in the *other* class, the better the model will learn. If not enough samples are assigned to this class, images that do not contain key planes may be labeled as being from such classes. Hence, it is crucial to have a proper value for the number of items in class *other*, and this value will be empirically determined. After these transition samples are extracted, the human experts will again check the samples to ensure that key planes would not be included by mistake. DSIT will try different state-of-the-art DL pre-trained algorithms on the data set with the plane views. The training will take place only on images, not on video files at this stage. After training, the model that proved to be the most accurate on the validation set will be saved, and it will be included in an application that will be able to deal with video files.

#### IV. Experiments

All the recent DL entries will be tailored and tested on the current scenario of key view identification. Their prediction results will be analyzed compared to the ground truth marked by the OBC. The metrics concern accuracy, precision, recall, and F1-score. A hierarchy will be built based on statistical testing, and the best algorithm will represent the AI module for this scenario. Different architectures can be tried. Some have a relatively small number of layers, and they are faster as concerns running time. Others are very deep, meaning that they have a high number of layers hence they take longer to train but are potentially more accurate. It is essential to be fast in the testing stage for the final trained model used in practice, as the training model would not be later re-initiated. Although the more complex models still run slower in the testing phase than those with fewer layers, the differences are minimal. However, the current task needs to be thoroughly tested since it might be the case that shallow models also lead to accurate results and, if this is the case, they will be preferred. The accuracy-speed equilibrium will be considered when ranking the approaches since the system will finally perform on a video.

Once a new video is available in practice, the model chosen for the task will highlight each key feature and the probability/certainty. Additionally, the final application will present a graphical and numerical report showing the number of frames with key planes identified and the indication of the certitude it has for them. Finally, the OBC physicians will validate all the intermediary findings at frame level and the meaningfulness of the video labeling.

#### V. Sample size calculation

As opposed to classical statistics, for machine learning in general, but for deep learning tasks that involve image classification in particular, there is not a general pre hoc rule for calculating the sample size. The pre hoc model-based approaches rely on the features of the algorithms taken into consideration. We underline that the approaches to be used are non-linear, in fact they are from the deep learning family. The classification accuracy will continue to improve as more data is included in the training process, as opposed to standard machine learning algorithms, where the accuracy reaches a plateau when the data attains a certain threshold. The statistical heuristic methods often take into account the number of classes, the number of input features and the number of parameters of the model. However, considering that the number of parameters of a deep learning approach is usually of many millions and that for each distinct parameter there are usually tens of samples necessary, a statistical heuristic method becomes unusable. A rule of thumb in deep learning is to have 1000 samples per class, as used in the ImageNet dataset pioneered in the Large Scale Visual Recognition Challenge 2012. The number of samples is smaller than what a heuristic estimate would indicate, since transfer learning will also be employed and additionally the data set will be artificially enlarged via image augmentation. Accordingly, it is intended to have at least 6000 images (around 1000 per class) within our data set, which could be extracted from approximately 300 ultrasound video files. We intend to make a post hoc sampling estimation study by considering subsets of the data for training and observing the results on the same test set.

### Outcome measures

#### Primary outcome

The primary outcome of this study is an IS that can assist the early-stage sonographers in helping and training for accurate detection of the four first-trimester cardiac key-planes.

#### Secondary outcomes

The increase in the rate of satisfactory evaluations of the heart key-planes in first trimester scans by inexperienced and newly trained sonographers.The optimization of the ultrasound clinical workflow using AI as an assistant for the FE practice through a time- efficient video labeling, i.e., a video frame processed in less than 20 milliseconds. Several options could be tried to achieve this, and the optimal decision will perhaps include all of them. We intend to vary the preprocessing options since some might be time-consuming. Another option refers to resizing the input images to a smaller dimension as long as the accuracy does not significantly decrease since they are faster to process when the size of the input data is reduced. Changing the deep learning model architecture to one with fewer layers would also reduce the amount of time for the processing of video frames.A reduced rate of diagnosis discrepancies between evaluators with different experience.

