#### Interventions

All pregnant women that meet the inclusion criteria will be examined by trained sonographers with at least three years of experience with fetal cardiac imaging.

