### Statistical methods

There will be several deep learning architectures trained on the obtained data set. In order to select the most prolific one and be assured that its results are not based on chance, the performance of the different models tried in terms of the considered metrics will be assessed under random sub-sampling cross-validation with multiple repetitions and the significance in the difference of the results will be checked via a Wilcoxon signed-rank test.

The performance of the computational models on videos taken by inexperienced sonographers will be statistically assessed compared to the results on scans where an expert made the examination. In order to achieve this, two sets of video scans will be completed, one containing video files made by experienced sonographers and the other made by inexperienced ones. The frames that the computational model labels will be extracted from the scans, and the experienced physicians will validate their predictions for both types of data. A t-test and a Mann-Whitney test for independent test samples will be used for verifying the differences in the results on the two sets.

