### Study limitations

A limited number of ultrasound devices types and techniques used to acquire the ultrasound sweeps may represent an impediment to large-scale implementation of the study results. The imaging of other ultrasound systems than the ones used to complete the study may differ significantly in the color format, and the performance of the software could be lower. We address this issue by using several color and directional power Doppler techniques and different generations of equipment in the study.

According to the study design, we will include in the study normal hearts; thus, the accuracy for detection of CHD cannot be evaluated from these data.

FE is feasible and efficient during the first trimester. Still, the continuous training process is impaired by the lack of specialists or their limited availability. Therefore, in our study design, the sonographer benefits from a second opinion provided by the developed software, which may be very helpful, especially if a more experienced colleague is unavailable. In addition, the software may be implemented on the ultrasound device so that the process could take place during the live examination.

Also, this software may help improve heart scanning skills because the operator will be stimulated to obtain satisfactory images regarding the key-planes of the cardiac sweep.

This study will provide insight into the feasibility of automatization of the 2D-FE. The aim is to provide a more early and accurate prenatal diagnosis of CHD to improve the treatment options for parents: pregnancy termination or birth in a specialized center. This will ultimately improve the couple’s satisfaction regarding the first-trimester anomaly scan performance, infant survival rates, and the quality of life of the newborns.

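### Two of the three secondary outcomes are changes in sonographer performance, but both planned comparisons judge the model, so neither outcome can be estimated as planned

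*Protocol article*

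**What the plan says.** Outcomes are numbered here in the order in which the article lists them.

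- **Primary outcome section:** "The primary outcome of this study is an IS that can assist the early-stage sonographers in helping and training for accurate detection". The detection target is the set of four key planes. No measure is named in that section.
- **Secondary outcome 1:** "The increase in the rate of satisfactory evaluations of the heart key-planes in first trimester scans by inexperienced and newly trained sonographers".
- **Secondary outcome 2:** a time-efficient workflow, made concrete as "a video frame processed in less than 20 milliseconds".
- **Secondary outcome 3:** "A reduced rate of diagnosis discrepancies between evaluators with different experience".
- **Statistical methods, comparison A:** several architectures are compared by repeated random sub-sampling, with a Wilcoxon signed-rank test.
- **Statistical methods, comparison B:** "The performance of the computational models on videos taken by inexperienced sonographers will be statistically assessed" against the results on expert-acquired scans. It uses two independent sets of videos, a t-test and a Mann-Whitney test, and experienced physicians validate the model's labels.
- **Interventions:** all women who meet the inclusion criteria "will be examined by trained sonographers with at least three years of experience with fetal cardiac imaging". The Abstract also ties inclusion to the availability of experienced sonographers.
- **Study limitations:** "we will include in the study normal hearts; thus, the accuracy for detection of CHD cannot be evaluated from these data". The same section says that, within the design, the sonographer gets a second opinion from the software.

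**The concern.** An increase, or a reduction, attributed to a decision-support system is a contrast between working with it and working without it. If no such contrast is planned, no choice of test can supply the estimate.

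The stake is the conclusion the study may draw. Comparison B can show whether the model copes as well with sweeps from inexperienced operators as with sweeps from experts. That is a useful robustness result, but it says nothing about whether the inexperienced operators do better because of the model. With the outcomes worded as they are, the robustness result is the nearest thing to an answer and could be mistaken for one.

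The operator statements add a practical problem. Comparison B needs videos that the Interventions section, read literally, does not provide for.

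**Working it through.** There is no figure to reproduce. The 6000-image target under Sample size calculation is a rule of thumb for training and does not bear on this point. The check sets each outcome beside each planned comparison.

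**Step 1. What each outcome requires.**

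- Secondary 1: let p be the rate of satisfactory key-plane evaluation by inexperienced sonographers. The outcome is p(with system) − p(without system).
- Secondary 2: processing time per frame, compared with 20 ms. No user is needed.
- Secondary 3: let d be the rate of discrepancy between evaluators of different experience. The outcome is d(without system) − d(with system). This needs evaluators of differing experience judging the same material under both conditions.

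**Step 2. What each comparison delivers.** Let M be the model's performance against expert judgement.

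- Comparison A: M(architecture i) − M(architecture j). No sonographer is under test.
- Comparison B: M(videos by inexperienced operators) − M(videos by experienced operators). The model is under test; the operator only acquires the video.

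**Step 3. Match.**

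| Outcome | Comparison A | Comparison B |
|---|---|---|
| Secondary 1, change in p | no | no |
| Secondary 3, change in d | no | no |

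Neither p nor d appears in A or B. A zero difference in B is compatible with any value of p(with system) − p(without system), because B never observes p under either condition. By count, 0 of 2 comparisons contrast users with and without the system, and 1 of 2 uses videos from inexperienced operators at all.

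**Step 4. Could the procedures supply the contrast?** Study design and setting describes a model-training part and a model-testing part. From Recruitment through Experiments, the steps are acquiring sweeps, labelling frames, training, testing and expert validation of labels. None has a sonographer scanning or reading with the system and again, or in parallel, without it. The second opinion mentioned under Study limitations has no matching procedure or analysis.

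**Step 5. The primary outcome.** Data preprocessing sets a 60/20/20 split by patient. Experiments compares predictions with expert ground truth on accuracy, F1, recall and precision. Detection performance is therefore measured, but those metrics are introduced to rank algorithms and none is tied to the primary outcome. Data preprocessing also compares the three image-preparation scenarios on both the validation and the test sets. Test-set performance would then be partly a result of selection if it were used as the primary measure without change.

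**Step 6. Operators.** Interventions gives at least three years of fetal cardiac imaging experience for all included women. Statistical methods requires a set of videos made by inexperienced operators. Both cannot hold for the same women unless one statement is limited in scope, and the article does not limit either.

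**The case against.** The strongest reply is that this is a condensed article about developing a system. The Abstract says that the primary objective is to develop it, and metric choice and success thresholds are commonly left to a fuller document. That stands for the missing threshold. It also tempers the point on the primary outcome: a reader might infer that this outcome has no estimator and cannot fail, or that only the 20 ms outcome is answerable. The documents do not support that, because key-plane detection is measured against expert ground truth on a test set. What is missing is the designation. The reply does not rescue secondary outcomes 1 and 3, because the article states both the outcomes and the analyses and they address different questions. An analysis plan cannot estimate an effect of use from a design in which nobody is described as using the system.

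Three further objections have force.

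- **Operators.** A reader might infer that every scan is done by experts. Statistical methods plans inexperienced-operator videos, the Interventions statement may have been meant for training data, and Data set organization adds recordings from 2018 onward with no operator restriction. The supportable point is a conflict between two sections.
- **Normal hearts.** A reader might infer that diagnostic disagreement cannot be studied at all. Evaluators can still differ on a normal heart, through false suspicion or a view judged inadequate. What is excluded is disagreement about real defects, and the article already says that accuracy for these cannot be evaluated.
- **Reporting.** Nothing in the article says that equal model performance on the two sets will be presented as improvement in inexperienced operators. That is a risk, not a stated intention.

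The cross-sectional design is not itself the fault, since stored cross-sectional videos could support an aided-versus-unaided reading.

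**Conclusion.** The mismatch is real and lies in the plan as written. Two of three secondary outcomes are changes in human performance, and neither planned comparison can estimate them. Secondary outcome 2 is unaffected. The primary outcome is measurable but worded as a product, with no designated measure. The operator statements in Interventions and Statistical methods contradict each other and leave the data source for comparison B unclear.

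The conclusion uses no power, alpha or effect-size assumption. It rests on two readings: that an increase and a reduced rate are meant as effects of the system, as the Aim and the primary outcome suggest, and that the article's account of procedures and comparisons is complete as to who uses the system. If a user study exists elsewhere, the article should say so.

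**What to change.** 1. **Secondary outcome 1.** Restate it as system performance on sweeps acquired by inexperienced versus experienced sonographers. Comparison B already estimates this.
2. **Secondary outcome 3.** Drop it or defer it to a later user study. Rewording it as agreement between evaluators would not be enough, because no evaluators of differing experience are planned to read the same sweeps.
3. **Alternative to 1 and 2.** Keep both as user-benefit outcomes only if an aided-versus-unaided reading of stored sweeps is added, with the order randomised or a washout between readings, analysed as paired data by reader. A fixed unaided-then-aided order would mix the system's benefit with the effect of a second look. Such a study covers reading and not acquisition, and the outcome wording should say so.
4. **Primary outcome.** Tie it to key-plane detection performance on the held-out test patients and designate the measure. Make all architecture and preprocessing choices without those patients, which means removing the test set from the scenario comparison in Data preprocessing.
5. **Operators.** Reconcile Interventions (and the Abstract) with Statistical methods: state who acquires each set of sweeps and from which women.

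Items 1, 2 and 5 are wording changes. Item 4 also changes how the test set is used. No extra scanning is needed for either the restatement or the reading study. The cost is narrower claims about benefit to sonographers, plus reader time if item 3 is chosen.

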### Statistical methods

There will be several deep learning architectures trained on the obtained data set. In order to select the most prolific one and be assured that its results are not based on chance, the performance of the different models tried in terms of the considered metrics will be assessed under random sub-sampling cross-validation with multiple repetitions and the significance in the difference of the results will be checked via a Wilcoxon signed-rank test.

The performance of the computational models on videos taken by inexperienced sonographers will be statistically assessed compared to the results on scans where an expert made the examination. In order to achieve this, two sets of video scans will be completed, one containing video files made by experienced sonographers and the other made by inexperienced ones. The frames that the computational model labels will be extracted from the scans, and the experienced physicians will validate their predictions for both types of data. A t-test and a Mann-Whitney test for independent test samples will be used for verifying the differences in the results on the two sets.

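### The between-model Wilcoxon test cannot, by itself, give the stated assurance that the selected model's results are not due to chance

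*Protocol article*

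**What the plan says.** Under Statistical methods the Protocol article states: "There will be several deep learning architectures trained on the obtained data set". The purpose of the comparison is given as "In order to select the most prolific one and be assured that its results are not based on chance". The means are "random sub-sampling cross-validation with multiple repetitions", after which "the significance in the difference of the results will be checked via a Wilcoxon signed-rank test". Section IV. Experiments adds: "A hierarchy will be built based on statistical testing, and the best algorithm will represent the AI module for this scenario". The same section lists the performance measures, taken against expert ground truth: "The metrics concern accuracy, precision, recall, and F1-score".

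No chance-level or trivial comparator is named. The number of models, the number of repetitions and the significance level are not given either. The other tests under Statistical methods (t-test and Mann-Whitney) compare scans by experienced and inexperienced sonographers, so they do not compare the system with chance.

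**The concern.** The sentence names a claim and the procedure meant to support it, and the two do not match on either reading of chance.

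- **Chance as performance without real signal.** A paired test between two models has no chance-level reference. Two uninformative models that differ in their label habits can be declared different, while two excellent models that are equally good usually are not. The p-value does not track the claim in either direction.
- **Chance as a lucky lead.** A between-model test is relevant here, but its reference distribution is for one pair fixed beforehand. The plan picks a winner from several models after seeing the results and builds a hierarchy by testing.

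The primary outcome is the system itself, and the Study strengths section promises statistical validation at each step. A between-model p-value could be taken for that validation, which it is not.

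**Working it through.** The document gives no figure for this comparison, so there is none to reproduce.

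**Inputs from the document**
- The class *other* has "around 30% more samples than in the class with the most images" (III. Frame Classification).
- For the data set, "it is intended to have at least 6000 images (around 1000 per class) within our data set", from about 300 videos (V. Sample size calculation).
- The test share is 20%, split by patient (II. Data preprocessing).

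**Assumed:** two-sided alpha 0.05; 10 or 30 repetitions; 3, 5 or 8 models; four key-plane classes of equal size. Simulation A uses 1,060 test images per repetition (20% of 5,300). Simulation B uses 300 patients with 20 frames each, so 60 patients and 1,200 frames per test set.

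**1. Rejection without learning.** With key-plane classes of 1,000 and *other* at 1,300, always answering *other* is correct in 1300/5300 = 24.5% of frames. Uniform guessing among five classes is correct in 20%. With 1,200 frames, the standard error of the difference in one repetition is about √(0.245×0.755/1200 + 0.2×0.8/1200) = 0.017. The gap of 0.045 is thus about 2.7 standard errors in every repetition, and nearly all paired differences have the same sign. Both simulations rejected in 100% of studies, with 10 and with 30 repetitions.

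**2. No rejection when both work.** Two models at 90% accuracy each: rejection in 4-5% (simulation A).

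**3. All models guessing equally.** Each at 20%, fresh guesses in each repetition: a given pair is rejected in 4.0-5.7% (simulation B), about the nominal level.

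**4. Winner picked afterwards, equal models, independent repetitions, no correction**

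| Models | Winner better than at least one rival, A | Same, B | Winner better than runner-up, B |
|---|---|---|---|
| 3 | 11-13% | 10-11% | 1.1-1.3% |
| 5 | 21-27% | 24-27% | 0.3-0.5% |
| 8 | 43-46% | 46-50% | 0-0.2% |

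The winner beat all rivals in at most 0.7%. As a rough guide to a full hierarchy, 1 − 0.95^m over m = 3, 10 and 28 pairs gives 14.3%, 40.1% and 76.2%. Pairs that share a model are not independent, so this is only an approximation.

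**5. Overlapping sub-samples.** Repeated random sub-samples share patients, so the repetitions are not independent. Simulation B re-scored fixed predictions on random 20% subsets of the same 300 patients. One pair of equal models was rejected in 23-28% (10 repetitions) and 45-51% (30 repetitions), before any selection. At 30 repetitions, winner versus runner-up rose to 17-32%. Bonferroni over all pairs still left winner versus at least one rival at 65% (3 models), 80-82% (5) and 92% (8). A further check of a Friedman test followed by Holm on overlapping sub-samples gave 30-86% false positives. Correcting for the number of comparisons does not repair dependence between repetitions.

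**The case against.** The strongest reply is that the sentence is about selection, so its natural meaning is that the winner's lead is not an accident of one split. A between-model comparison over repeated splits does address that. Performance above chance would be visible elsewhere: accuracy, precision, recall and F1 are measured against expert labels, patients are kept in one set only, and physicians validate the output. Per-class recall would expose a model that always answers *other*. Selection also does not rest on the p-value alone, since validation accuracy and speed count and accurate shallow models are preferred. Much of this stands and limits how serious the point is. It does not turn the named test into evidence of above-chance performance.

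A reader might infer more than the documents support:
- *The test rejects whenever no model has learnt.* It does not. Models that guess equally well are rejected at about 5% if repetitions are independent. It can reject when non-learning models differ from each other.
- *The winner's lead is overstated against every rival.* With independent repetitions the inflation concerns the winner against at least one rival. Against the runner-up or against all rivals, the rate is well below 5%.
- *The lack of a multiplicity correction is itself a fault.* A correction may be given in the analysis plan, which is not shown.
- *The p-value will be reported as proof that the system works.* The article does not say so, and no success criterion depends on the test.

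**Conclusion.** The point holds in limited form. The article gives a test between models a claim that the test does not address, and an analysis plan could not cure this without changing the sentence. The p-value can be significant when neither model has learnt (100% in the example of 24.5% against 20%), and it is usually non-significant when two models are equally good (4-5%).

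On the lucky-lead reading, a false result against at least one rival occurs in about 10-50% of studies for 3 to 8 equal models with independent repetitions, and rarely against the runner-up. Overlap between sub-samples raises these rates, and standard multiplicity corrections on the repetitions do not bring them back. The rates depend on the assumed numbers of models, repetitions and frames per patient; the 24.5% depends on equal key-plane classes. The mismatch between test and claim depends on none of these. The change is worth making because it is cheap and would supply the assurance the plan wants.

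**What to change.** 1. Describe the Wilcoxon result only as an exploratory comparison used to rank models, and remove the link to results not being due to chance.
2. Base that statement on the locked model, evaluated once on the held-out 20% of patients, against the always-*other* classifier. Report the difference in one named metric, macro-F1, with a bootstrap interval that resamples patients. These patients must play no part in choosing architecture or preprocessing; section II. Data preprocessing now compares the preprocessing scenarios on the test set as well, and would have to use the validation set only.
3. Always-*other* is a low bar on macro-F1: its F1 for *other* is 2×0.245×1/(0.245+1) = 0.394 and zero for the other four classes, so macro-F1 is 0.394/5 = 0.08. Guessing at class frequencies gives each class an F1 equal to its share, so macro-F1 is 1/5 = 0.20. Report the model against that value too.
4. If superiority over other architectures is claimed, use the same held-out patients, with paired patient-level bootstrap differences and Holm correction.

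The cost is a few lines of code and a few sentences. The downside is that fewer differences between architectures will be called significant. With about 60 held-out patients (20% of 300, if each video is one patient), intervals will also be wider than frame-level ones.
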